
### Common procedural protocol

All patients underwent coronary angiography and/or percutaneous coronary intervention via a transradial approach. A uniform set of pre-procedural and intra-procedural measures, designed to minimize vascular injury and the risk of radial artery occlusion, was applied to all participants before randomization and hemostasis. This standardized protocol was implemented in accordance with contemporary best practices as established in large randomized trials [1].

Arterial Access and Procedure: Vascular access was obtained using a 6-French Glidesheath Slender introducer (Terumo, Tokyo, Japan). The choice of access side (left or right wrist) was at the operator’s discretion based on anatomical and clinical considerations. Following sheath insertion, all patients received an intravenous bolus of unfractionated heparin (5,000 IU), with additional boluses administered if needed to maintain an activated clotting time (ACT) between 250 and 300 seconds. To mitigate radial artery spasm, an intra-arterial vasodilator cocktail containing verapamil (5 mg) and/or nitroglycerin (100–200 μg) was administered through the sheath.

Pre-Hemostasis Assessment: Immediately following the coronary procedure and prior to the application of any hemostatic device (and thus prior to group assignment), patency of the access artery was confirmed using the reverse Barbeau test [17]. This step ensured a documented baseline of radial artery flow for all enrolled subjects.

### Criteria for discontinuing or modifying allocated intervention

A participant’s allocated intervention (either the novel system or traditional hemostasis) will be discontinued or modified prior to the planned time if: (1) Uncontrollable bleeding or a major vascular complication occurs; (2) The participant experiences intolerable pain or discomfort and requests early device removal; (3) Signs of distal limb ischemia or nerve injury develop; (4) Any other serious adverse event deemed by the treating physician to be related to the hemostasis method and necessitating its cessation.

### Intervention: Operating procedure of the system

The standardized operational procedure for the balloon pressure monitoring system is summarized in Fig 4 (left panel) and detailed as follows:

Initial compression: Immediately following sheath removal, the balloon is inflated to a target pressure of 260 mmHg. (This pressure, derived from a pre-trial pilot study (n = 32), ensures reliable immediate hemostasis with no associated neurovascular or skin injuries.)Individualized minimum effective hemostatic pressure titration: The balloon pressure is gradually decreased until slight oozing is observed at the puncture site. Then, the pressure is incrementally increased in steps of 20 mmHg until bleeding ceases. This value is recorded as the patient’s initial hemostatic threshold.Phased decompression and monitoring: At 30 minutes post-procedure, the pressure is adjusted to 60 mmHg (an intermediate value based on the hemostatic threshold, with fine-tuning for bleeding status). At 60, 90, and 120 minutes post-procedure, pressure is reduced by 30 mmHg at each interval until it reaches zero.Bleeding management: If bleeding occurs at any stage, pressure is increased in 20 mmHg steps until hemostasis is reestablished.Documentation: All pressure values, operation times, and involved personnel are recorded throughout the procedure to ensure traceability.

(The parameters for this procedure—including the initial pressure, titration step, and decompression schedule—were derived from a preceding pilot study.)

### Control group intervention: Standardized traditional patent hemostasis

#### Rationale for comparator selection.

Traditional patent hemostasis was selected as the comparator because it represents the current international consensus and standard-of-care practice for radial artery occlusion prevention following transradial procedures. Comparing the novel balloon pressure monitoring system against this established benchmark allows for a direct assessment of its potential incremental efficacy and safety benefits in a clinically relevant context. To ensure a fair comparison, the control group will undergo a standardized traditional patent hemostasis protocol using a balloon-based radial artery compressor, as detailed below and summarized in Fig 4 (right panel).

#### Operational protocol for traditional patent hemostasis.

Initial hemostasis: after sheath removal, inflate the balloon compressor with an initial 18 mL of air for primary hemostasis [2,18].Patency Confirmation (Reverse Barbeau Test): Gradually decompress the balloon until slight oozing is observed at the puncture site, then inject 1–2 mL of air to re-establish the hemostasis. Subsequently, manually compress the ulnar artery for 2 minutes while continuously monitoring the pulse oximetry waveform of the ipsilateral thumb. If the waveform remains present with a stable amplitude throughout the entire compression period (corresponding to Barbeau classification Type A or B), the radial artery patency under compression is confirmed; if the waveform disappears (corresponding to Type D or partial Type C, indicating occlusive compression), immediate further decompression must be conducted until the waveform is restored [2,18].Phased decompression: at 30 minutes post-procedure, release 1 mL of air. At 60- and 90-min post-procedure, release 3 mL of air at each interval. At 120 min post-procedure, remove the compression device [2,18].Bleeding management and documentation: if bleeding occurs, reinflate with an appropriate volume of air to achieve hemostasis, and record the time of intervention and personnel involved [2,18].

Statistical parameters: The sample size was calculated using PASS 15.0.5 software with a two-sided α error of 0.05 and a β error of 0.2 (corresponding to 80% statistical power). Based on a reported 24-hour radial artery occlusion (RAO) incidence of 4.3% in the control group and a predefined superiority margin of 3.3% absolute risk reduction, the initial required sample size was 736 patients with a 1:1 allocation ratio between the two groups. Accounting for an estimated 10% dropout rate, the final planned sample size was set at 818 patients (409 per group).

### Inclusion and exclusion criteria

The inclusion and exclusion criteria (Table 1) were defined to enroll a representative patient population with indications for coronary angiography that reflect routine clinical practice, ensuring the external validity of the trial for real-world application.

**Table 1 pone.0350563.t001:** Inclusion and exclusion criteria.

*Inclusion Criteria*
Aged 18 years old or over and less than 80 years old
Patients undergoing coronary angiography in the Department of Cardiology
Patients with clear consciousness and certain ability to understand and express
Patients who are willing to participate in the study and provide written informed consent
Use of antiplatelet drugs: 300 mg aspirin enteric-coated tablet + 180 mg ticagrelor tablet or 300 mg Clopidogrel bisulfate tablet one day before surgery; On the day of surgery, 100 mg aspirin enteric-coated tablet + 90 mg ticagrelor tablet or 75 mg Clopidogrel bisulfate tablet.
*Exclusion Criteria*
Patients with upper limb disability or deformity
Patients with local skin or tissue edema or infection
Patients with abnormal coagulation function or severe complications who have had two or more ipsilateral radial artery punctures
The puncture point is not 1–2 cm below the palm stripe

### Follow-up plan

Patients will be followed for prespecified endpoints until hospital discharge, with no scheduled post-discharge follow-up for primary endpoints. Consenting patients will be invited to an optional 30-d outpatient follow-up visit for radial artery patency assessment via ultrasound, which will serve as an exploratory endpoint to evaluate the persistence of hemostasis effects and late vascular remodeling.

### Endpoints

#### Primary endpoint.

The primary endpoint was set as the incidence of forearm RAO at 24 hours post-procedure—the consensus-recommended timepoint for early patency assessment—assessed by a blinded independent investigator using Doppler ultrasound. Forearm RAO is defined as the absence of an anterograde flow signal in the distal radial artery.

#### Secondary endpoints.

The secondary endpoints were defined as follows:

Incidence of access-site related vascular complications, such as radial artery perforation, arteriovenous fistula, pseudoaneurysm;Incidence of bleeding events, classified per standardized bleeding scales for cardiovascular trials;Objective measures of hemostasis convenience, operationally defined to reduce measurement variability, include: i) total hemostasis time, which is the cumulative duration from arterial sheath removal to complete hemostasis device removal and puncture site hemostasis confirmation, with only active operation and assessment time counted (fixed 30/60/90-min observation periods are excluded to minimize variability); and ii) operator workforce input, which is measured via two metrics (with CRF-designed recording templates for feasibility): peak and active operator number. The peak operator number is the maximum number of healthcare personnel simultaneously performing hands-on tasks (pressure adjustment, bleeding assessment, data recording) at any stage. The active operator time is the sum of durations each operator spends on direct hands-on tasks, recorded via start/stop timestamps for each personnel.

#### Exploratory endpoints.

The exploratory endpoints are the incidence of forearm RAO at 30 d post-procedure in consenting patients, and the operator-perceived ease of use, which is assessed via a validated brief questionnaire completed immediately after each hemostasis procedure.

Given the anticipated low incidence of individual major vascular complications, analyzes of these events will be primarily descriptive to document the overall safety profile. All such events will be identified and characterized according to the standardized safety assessment procedures detailed in the Safety Assessment and Harms section.

### Safety assessment and harms

#### Definition.

All adverse events (AEs) will be recorded from the time of informed consent until hospital discharge. AEs will be classified as serious (SAEs) according to ICH-GCP guidelines. Bleeding events will be defined and graded according to the Bleeding Academic Research Consortium (BARC) criteria. Vascular complications (e.g., pseudoaneurysm, arteriovenous fistula) will be diagnosed by clinical assessment and confirmed by Doppler ultrasound.

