### Study design and purpose

This is a single-center, prospective, randomized controlled trial (RCT) designed to compare the safety and efficacy of our novel system versus traditional patent hemostasis for post-coronary angiography radial artery hemostasis, with preventing forearm RAO as the primary goal. As the first large-scale RCT focusing on digital manometry-guided hemostasis for RAO prevention, this study plans to enroll 818 eligible patients, who will be randomly assigned in a 1:1 ratio to either the balloon pressure monitoring group or the traditional hemostasis group. Allocation concealment will be ensured using computer-generated random sequences and sequentially numbered, opaque sealed envelopes. To minimize bias, independent investigators assessing primary and secondary endpoints will be blinded to patient group allocations. Follow-up will continue until hospital discharge, with an optional 30-day outpatient follow-up for exploratory RAO assessment.

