#### 3. Endpoint adjudication committee.

Composition: This committee includes two vascular ultrasound specialists and one interventional cardiologist, all of whom are blinded to treatment group allocation.

Roles & Responsibilities: It independently adjudicates all primary endpoint events (24-hour radial artery occlusion) and predefined serious vascular complication endpoints (e.g., pseudoaneurysm, arteriovenous fistula). All imaging and clinical data for suspected endpoint events undergo centralized, blinded assessment by this committee based on pre-specified standardized definitions. Its adjudication is final.

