#### Blinding implementation.

Given the distinct nature of the two interventions, blinding of the operators performing hemostasis or the patients is not feasible. Therefore, to minimize assessment and measurement bias, the following blinding measures are implemented: 1) blinding of endpoint assessors, with the primary endpoint (24-hour forearm RAO) assessed by an independent, group-blinded investigator using Doppler ultrasound; and 2) blinding of data analysis, with statistical analysis conducted by an independent statistician blinded to group allocation.

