#### Unblinding procedure.

Given that the treating physicians are unblinded, emergency unblinding for clinical management is not required. However, the blinding for the endpoint assessors and statisticians will be maintained throughout the trial. In the exceptional circumstance that unblinding of a participant’s allocation is deemed necessary for the safety assessment by the DSMB or for regulatory reasons, a formal request must be submitted to and approved by the Steering Committee. The unblinding will then be performed by the independent statistician who holds the allocation list, and the date and reason will be fully documented.

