#### Assessment.

AEs will be assessed systematically through:

Active questioning and physical examination of the access site at predefined time points during hemostasis and prior to discharge.Monitoring of all spontaneously reported symptoms by participants.Review of medical records and laboratory values for any potential signs of harm.

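### Access-site vascular complications enter the incidence endpoint only if someone first suspects them clinically, probably unblinded, while the blinded 24-hour Doppler is not assigned to look for them

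*Protocol article*

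**What the plan says.** The Secondary endpoints section lists "Incidence of access-site related vascular complications, such as radial artery perforation, arteriovenous fistula, pseudoaneurysm". The Exploratory endpoints section expects few major vascular complications, makes their analysis mainly descriptive, and refers to the safety section for how they are identified. There, the Definition paragraph says such complications "will be diagnosed by clinical assessment and confirmed by Doppler ultrasound".

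The Assessment paragraph makes detection systematic: "Active questioning and physical examination of the access site at predefined time points during hemostasis and prior to discharge", together with spontaneous reports and review of records. On the Endpoint adjudication committee, the article says: "All imaging and clinical data for suspected endpoint events undergo centralized, blinded assessment by this committee".

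On blinding, Study design and purpose says that "independent investigators assessing primary and secondary endpoints will be blinded to patient group allocations". Blinding implementation says that "blinding of the operators performing hemostasis or the patients is not feasible", and the one assessor it names as blinded is the assessor of 24-hour radial artery occlusion (RAO). The Unblinding procedure opens: "Given that the treating physicians are unblinded, emergency unblinding for clinical management is not required".

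The primary endpoint is "assessed by a blinded independent investigator using Doppler ultrasound" at 24 hours. Its definition concerns antegrade flow in the distal radial artery.

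**The concern.** An incidence endpoint should count the lesions that occur, by a method that works the same way in both arms. Here a lesion must be suspected clinically before Doppler is used, and must be suspected before the committee sees it. The committee can reject a suspected case but cannot add one that was never raised, so blinded adjudication protects only one side of the count.

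Two things are at stake. Silent lesions are lost, which understates incidence in both arms. And if the threshold for suspicion differs by arm, the safety comparison of a new device moves with that threshold, and adjudication cannot correct it. Meanwhile a blinded Doppler of the same artery is planned at 24 hours, and nothing in the article assigns that examiner to look for these lesions.

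**Working it through.** **Plan's own figure.** The article gives no rate for vascular complications. The only relevant figure is the number per arm (Sample size calculation), which reproduces. With RAO of 4.3% and 1.0%, two-sided 0.05, 80% power and unpooled variance:
- (0.043 × 0.957 + 0.010 × 0.990) × (1.960 + 0.842)² / 0.033² gives 368 per arm, or 736 in total.
- 736 / (1 − 0.10) = 818, or 409 per arm.

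This point does not affect that calculation.

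**Route into the count.**
1. Every patient is questioned and examined at set times (Assessment). This step is not selective.
2. Some patients are suspected of a complication. This step is selective.
3. Suspected cases go to Doppler for confirmation (Definition).
4. Suspected cases go to the blinded committee (Endpoint adjudication committee; Causality and adjudication).

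Steps 3 and 4 can only confirm or remove cases that passed step 2.

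**Who acts at step 2.** The article does not say who performs the access-site examination. Study design and purpose points to blinded assessors. These sections point the other way:
- Blinding implementation and Unblinding procedure leave operators, patients and treating physicians unblinded.
- Part of the examination takes place during hemostasis, with the device in view, and it includes questions to unblinded patients.
- Operator training has the operating staff trained to identify endpoint events.

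Unblinded first suspicion is therefore probable but not stated.

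**Illustrative size.** All rates here are assumptions. Let p be the true rate, equal in both arms, and s1 and s2 the share detected in each arm. Expected recorded cases per arm are 409 × p × s. The apparent relative risk is (p × s1) / (p × s2) = s1 / s2, whatever p is.
- True cases per arm: 409 × 0.005 = 2.0; 409 × 0.01 = 4.1; 409 × 0.02 = 8.2.
- Detection 50% in both arms: 1.0 to 4.1 recorded per arm over p = 0.5% to 2%; relative risk 1.0.
- Detection 40% against 60%: at p = 2%, 3.3 against 4.9 recorded; relative risk 0.67.
- Detection 30% against 70%: at p = 2%, 2.5 against 5.7 recorded; relative risk 0.43.

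Swapping the arms inverts the ratio (0.67 becomes 1.5). The article does not settle the direction. Active operator time is compared between arms, and Future research directions mentions lower staffing demand, which could mean less bedside contact with the new system. Closer attention to a novel device would act the other way.

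**The case against.** The strongest defence is that clinical diagnosis, Doppler confirmation and blinded adjudication together form a coherent definition of clinically evident complications. Analysis of major vascular complications is mainly descriptive, and the section on the primary and secondary endpoints bars confirmatory reading of secondary results. Counts will be small: about 7 against 4 events in 409 per arm gives a two-sided p of roughly 0.55. A scan checklist is also something an article may leave to the full protocol. All of this limits the consequence. It does not make the endpoint an incidence of these lesions, and a descriptive safety rate for a new device still needs comparable ascertainment in both arms.

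A reader might infer more than the article supports:
- *That the endpoint depends on who gets examined.* It does not, because questioning and examination are scheduled for everyone. Only suspicion and referral to Doppler are selective.
- *That the plan states detection is unblinded.* It does not. One section says secondary-endpoint assessors are blinded; the operational sections carry this through only for RAO. That conflict is the supportable finding.
- *That the safety comparison is biased.* No difference in detection is stated, and one assessment procedure is described for both arms. Equal under-detection leaves the relative risk at 1.0.
- *That every patient will have the 24-hour scan, and that it examines flow only.* The scan is planned, with 10% dropout allowed. The article gives the definition of RAO, not the full scan procedure.

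**Conclusion.** The point holds in limited form. As written, the secondary endpoint counts clinically suspected and then confirmed complications, so silent lesions can be missed and the blinded committee cannot recover them. First suspicion is probably unblinded, and the sections on blinding disagree for this endpoint.

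The size is unknown. The apparent relative risks of 0.67 and 0.43 rest on assumed detection of 40% against 60% and 30% against 70%, with equal true rates. If detection is equal, the only loss is understated incidence. The primary endpoint, its sample size and its test are untouched. The change is worth making because it is cheap and concerns the safety record of a new device; the trial's main conclusion does not depend on it.

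**What to change.** 1. In Secondary endpoints and in the Definition paragraph of the safety section, have the blinded examiner at the planned 24-hour Doppler record pseudoaneurysm and arteriovenous fistula at the access site (yes/no, image stored) in every patient scanned from the amendment onward.
2. Send any lesion found on that scan, as well as any suspected clinically, to the adjudication committee.
3. Report clinically evident and scan-only lesions separately, and flag patients enrolled before the change.
4. Keep the as-treated safety analysis set out under Analysis populations, with a table by randomised arm beside it.
5. Leave radial artery perforation on the clinical route.
6. Reconcile Study design and purpose with Blinding implementation: state who performs the access-site examination and whether that person is blinded.

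The cost is two extra fields and a slightly longer scan. Some subclinical lesions will be counted, which separate reporting handles. Recruitment began in September 2024 and is expected to end by May 2026, so ascertainment will be mixed across recruitment. The change reaches both randomised arms alike, but pooled rates need the before-and-after flag. The scan adds only lesions present at 24 hours; later ones, up to discharge, still depend on clinical suspicion.

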#### Assessment.

AEs will be assessed systematically through:

Active questioning and physical examination of the access site at predefined time points during hemostasis and prior to discharge.Monitoring of all spontaneously reported symptoms by participants.Review of medical records and laboratory values for any potential signs of harm.

#### Causality and adjudication.

The treating physician will initially assess the causality of all AEs in relation to the hemostasis procedure. All SAEs and predefined significant vascular complications will be reviewed and adjudicated by the blinded Endpoint Adjudication Committee (see Trial Oversight Structure).

#### Recording.

All AEs will be documented in the electronic case report form (eCRF) using standardized terminology.

### Statistical methods

#### Analysis populations.

The populations to be analyzed are as follows:

intention-to-treat population, which includes all randomized patients, analyzed according to their original treatment assignment, regardless of protocol deviations or crossovers, for the primary efficacy analysis;per-protocol population, which excludes patients with major protocol violations (e.g., significant hemostasis protocol deviation, use of contraindicated medications) or cross-group interventions, serving as a supportive sensitivity analysis;as-treated population, which comprises patients analyzed according to the actual hemostasis method received, for all safety analyzes.

